#### Additional exclusion criteria for healthy controls

2.3.3

Lifetime history of any psychiatric disorder (assessed using a structured clinical interview).First-degree relatives with a psychotic disorder.

Written informed consent will be obtained from all participants prior to enrollment. The study protocol was approved by the Ethics Committee of Wuxi Mental Health Center (Approval No: WXMHCIRB2025LLky094) and registered in the Chinese Clinical Trial Registry (ChiCTR2500110551).

### Procedures

2.4

All participants will complete a standardized assessment session consisting of demographic collection, clinical evaluations, interoceptive assessments, cognitive testing, and MRI scanning. All procedures will follow a fixed, predetermined order to minimize variability across participants. Assessments will be conducted by trained research personnel who are blinded to the study hypotheses.

#### Enrollment and screening

2.4.1

Participants with schizophrenia will be approached in clinical units, whereas healthy controls will be recruited through community advertisements and word-of-mouth. Eligibility screening will include demographic information, psychiatric and medical history, and MRI safety evaluation. Written informed consent will be obtained prior to participation.

#### Clinical and demographic assessments

2.4.2

Participants will undergo standardized clinical evaluations, including: PANSS, HAM-A, HAM-D, demographic information (age, sex, education and so on) and illness duration and medication status (patients only). All clinical ratings will be performed by two trained psychiatrists to ensure inter-rater reliability.

#### Cognitive assessments

2.4.3

Validated neuropsychological tests will be administered to assess cognitive performance: Trail Making Test (TMT): processing speed and executive function, Animal Fluency Test (AFT): verbal fluency and Digit Symbol Substitution Test (DSST): processing speed and attention. All cognitive assessments will be conducted in a quiet room to minimize distractions.

#### Interoceptive assessments

2.4.4

##### Heartbeat counting task

2.4.4.1

Interoceptive accuracy was assessed using the heartbeat counting task (HCT), a widely used behavioral paradigm for evaluating cardiac interoceptive perception (9, 25). Participants will complete three trials of varying durations (25 s, 35 s, 45 s). Instructions including Sit comfortably and remain still. Focus attention internally on heartbeat sensations. Avoid checking the pulse manually or using counting strategies. Report the number of perceived heartbeats after each interval. A 30-second practice trial will precede the formal task. Interoceptive accuracy will be calculated using the standard HCT formula.

##### Subjective interoceptive measures

2.4.4.2

Participants will complete two validated self-report questionnaires: MAIA and BPQ. Questionnaires will be administered using paper forms.

##### Time estimation task

2.4.4.3

Temporal perception was assessed using a time estimation task, a widely used paradigm in interval timing research and frequently applied in studies of predictive processing and schizophrenia (26, 27). Participants will also complete a time estimation task to assess temporal perception; a cognitive domain theoretically related to interoception and predictive processing. Time estimation is closely linked to interoceptive processing, internal predictive models, and disturbances in self-monitoring—domains known to be altered in schizophrenia (26).Participants will estimate the duration of predefined intervals (19 s, 37 s, 49 s) without counting, external cues, or motor strategies. They will verbally report their estimate after each interval.

Three practice trials will be administered before the formal assessment. Absolute estimation error (|estimated – actual|) and relative error [(estimated – actual)/actual] will be recorded for later analyses. For specific details, please refer to the **Supplementary Materials Text S1**.

#### MRI scanning procedures

2.4.5

MRI scanning will be conducted at Wuxi Ninth People’s Hospital, where MRI facilities are available for the present study.

Preparation.

Participants will remove all metal objects and complete MRI safety screening.Earplugs and padding will be provided to reduce noise and minimize head motion.Participants will be instructed to remain still, keep their eyes closed, and stay awake during resting-state scans.

Sequence Order.

A fixed acquisition order will be used:

Structural T1-weighted MRI (MPRAGE).Resting-state fMRI.Diffusion tensor imaging (DTI).

Total scanning duration will be approximately 30 minutes. MRI technicians will monitor data quality throughout acquisition. Parameter settings are detailed in **Supplementary Material Table 1**.

#### Data storage and quality control

2.4.6

All data will be coded with unique participant identifiers.Raw and preprocessed MRI data will be stored on secure, password-protected servers.Quality control will include checks for excessive head motion (>2.5 mm translation or >2.5°rotation).Datasets failing quality control will be excluded according to predefined criteria.

A detailed schedule of screening, baseline evaluation, behavioral testing, and MRI acquisition is presented in **Table 1**.

**Table 1 T1:** Study schedule of participant assessment.

Assessment domain	Screening	Enrollment/baseline	Assessment session	MRI session
Eligibility review	X			
Informed consent		X		
Demographics		X		
Medical/psychiatric history	X	X		
MRI safety screening	X			X
Clinical assessments			X	
PANSS			X	
HAM-A			X	
HAM-D			X	
Cognitive assessments			X	
TMT			X	
DSST			X	
AFT			X	
Interoceptive tasks			X	
Heartbeat Counting Task (HCT)			X	
MAIA			X	
BPQ (124-item)			X	
Time Estimation Task			X	
MRI scanning				X
T1-weighted structural scan				X
Resting-state fMRI				X
DTI				X
Data Quality Control				X

“X” indicates that the specified assessment is conducted at the corresponding study phase.

### Outcomes

2.5

#### Primary outcome

2.5.1

Interoceptive accuracy, assessed using the heartbeat counting task (HCT).

Interoceptive accuracy will be quantified using the standard HCT formula across the three intervals(25 s, 35 s, 45 s).

#### Secondary outcomes

2.5.2

Subjective interoceptive awareness, evaluated using MAIA and BPQ.Objective–subjective interoception relationships, including correlations between HCT accuracy and MAIA subscales and BPQ total/subscale scores.Clinical symptom severity, including PANSS, anxiety symptoms (HAM-A) and depressive symptoms (HAM-D).Cognitive performance, assessed by: Trail Making Test (TMT), Digit Symbol Substitution Test (DSST) and Animal Fluency Test (AFT).Associations among interoceptive measures (behavioral and subjective), clinical symptoms, and cognitive performance, including correlations between HCT/MAIA/BPQ and PANSS, HAM-A, HAM-D, TMT, DSST, and AFT scores.

#### Exploratory outcomes

2.5.3

Intrinsic neural activity, derived from resting-state fMRI metrics: Amplitude of Low-Frequency Fluctuations (ALFF), Regional Homogeneity (ReHo), Seed-based and ROI-to-ROI functional connectivity within interoception-related regions and networks, including: anterior insula, anterior cingulate cortex, amygdala, thalamo–cortical pathways and salience network nodes.Structural connectivity, assessed using DTI (DTI) indices: fractional anisotropy (FA), mean diffusivity (MD), radial diffusivity (RD), axial diffusivity (AD). Analyses will focus on interoception-related white-matter tracts, including fronto–limbic and thalamo–cortical pathways.Brain–behavior associations, examining relationships among: functional connectivity and DTI indices, interoceptive accuracy (HCT), subjective interoceptive awareness (MAIA, BPQ), clinical symptom severity and cognitive performance.Multimodal neural markers, identifying integrated structural–functional features associated with interoceptive dysfunction in schizophrenia.Time estimation performance, measured as absolute and relative error during the time estimation task, and its associations with interoceptive measures, clinical symptoms, and cognitive performance.

For specific details, please refer to **Supplementary Material Table 2**.

### Data analysis

2.6

#### Behavioral and questionnaire data

2.6.1

All behavioral, clinical, and questionnaire analyses will be performed using SPSS 26.0 and R 4.3.0.Group comparisons: Continuous variables (HCT accuracy, time estimation performance, MAIA, BPQ, TMT, AFT, DSST) will be compared using independent-samples t-tests or Mann–Whitney U tests for non-normal distributions. Categorical variables will be analyzed using χ² tests.All analyses will control for age, sex, years of education, and medication dosage (chlorpromazine equivalents). In analyses involving HCT accuracy, time estimation performance will additionally be included as a covariate to control for potential confounding effects related to temporal estimation ability. Additional sensitivity analyses will examine whether group differences in HCT accuracy remain significant after controlling for time estimation performance.Correlation analyses: Within each group, associations between interoceptive accuracy, subjective measures (MAIA/BPQ), PANSS scores, and cognitive performance will be examined using Pearson or Spearman correlations with FDR correction.

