#### Multimodal brain–behavior integration

2.6.5

Integrated analyses will evaluate relationships among neural indices (ALFF, ReHo, FC, FA, MD, RD, AD), interoceptive accuracy (HCT), subjective interoceptive awareness (MAIA, BPQ), clinical symptoms (PANSS, HAM-A, HAM-D), and cognitive performance.

Statistical methods will include multiple linear regression and partial correlations (controlling for covariates), with Bonferroni or FDR correction applied for multiple comparisons. The MRI preprocessing pipeline is illustrated in **Supplementary Figure 1**.

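### Section 2.6.1 names covariate-free tests for the primary HCT comparison but requires every analysis to be adjusted, so the primary analysis is not determined

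*Protocol article*

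**What the plan says.** The single primary outcome in section 2.5.1 is "Interoceptive accuracy, assessed using the heartbeat counting task (HCT"). Section 2.6.1 makes four statements about its analysis:

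- HCT accuracy is listed with time estimation, MAIA, BPQ and the cognitive scores as variables that "will be compared using independent-samples t-tests or Mann–Whitney U tests for non-normal distributions".
- "All analyses will control for age, sex, years of education, and medication dosage (chlorpromazine equivalents").
- Where HCT accuracy is involved, "time estimation performance will additionally be included as a covariate to control for potential confounding effects".
- "Additional sensitivity analyses will examine whether group differences in HCT accuracy remain significant after controlling for time estimation performance".

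The within-group associations in the same section "will be examined using Pearson or Spearman correlations with FDR correction", with no partial form named. A method that accepts covariates is named only in section 2.6.5, for the integration of imaging and behavior: "Statistical methods will include multiple linear regression and partial correlations (controlling for covariates"). Section 2.3 gives 30 participants per group, with controls matched on age and sex. Section 2.4.2 records medication status for patients only.

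**The concern.** An independent-samples t-test and a plain Mann–Whitney test have no place for a covariate, so the first two statements cannot describe the same analysis. The third and fourth do not fit together either. If every HCT analysis already includes time estimation, a sensitivity analysis that adds it repeats the main one. If the sensitivity analysis is to add something, the main one must leave time estimation out.

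Several different p-values could therefore each be presented as the primary result: t-test, Mann–Whitney, or a model with three, four or five covariates. They are not interchangeable. The t-test addresses a difference in means and the Mann–Whitney test the probability that one group exceeds the other. A model containing dose estimates a patient–control difference extrapolated to zero dose. An unsettled choice among them weakens the 5% error rate and leaves it unclear which analysis the stated power refers to.

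**Working it through.** **Inputs.** From the document: 30 + 30 participants, alpha 0.05 (sidedness not stated), power of approximately 80%, and an effect size called moderate with no number. Assumed, because the document gives no figures: normal outcomes, covariate–outcome correlations up to 0.3, and gamma-distributed doses with a coefficient of variation (CV) of 0.4 to 1.0 among patients, zero in controls, and no true dose effect.

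**1. The plan's own power figure.** For an unadjusted t-test, power comes from a noncentral t with 58 df and noncentrality d√(30/2).
- 80% two-sided requires d = 0.736; one-sided it requires d = 0.650.
- At d = 0.5, power is 48% two-sided and 61% one-sided.

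Without the numerical effect size the stated 80% can be neither confirmed nor refuted. Below, d = 0.736 serves only as the reference at which the unadjusted test has 80%.

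**2. Cost of adjusting for age, sex and education.** Residual df fall from 60 − 2 = 58 to 60 − 5 = 55.
- Covariates balanced between groups: power 0.7997, against 0.8004 for the t-test.
- Education differing by an assumed 0.8 SD: the variance of the group coefficient is multiplied by 1 + 0.8²/4 = 1.16. If education also explains some outcome variance (correlation 0.2 to 0.3), power is roughly 76–78%.
- Four covariates (time estimation added), unrelated to outcome and with chance imbalance simulated: about 78%.

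**3. Cost of adding dose.** With n per group, mean dose m and SD s among patients, and zero dose in controls, the group coefficient is the difference in means minus slope × m. Its variance is σ²(2/n + m²/(n·s²)), which is 1 + 1/(2·CV²) times the unadjusted variance.
- CV = 0.4: 1 + 1/0.32 = 4.125.
- CV = 1.0: 1 + 1/2 = 1.5.

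Simulating the full model (group, dose, age, sex, education, time estimation; 53 residual df) gives slightly larger factors, 4.88 and 1.72, because the other covariates and sampling variation in dose add to them. Simulated power at d = 0.736:

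| CV of dose | Power |
|---|---|
| 0.4 | 27% |
| 0.5 | 33% |
| 0.6 | 40% |
| 0.8 | 52% |
| 1.0 | 56% |

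**4. Type I error with a free choice.** Simulation with no group effect and no systematic education difference, 10,000 to 20,000 runs per scenario:
- Any single analysis fixed in advance: about 5%.
- Better of the t-test and the three-covariate ANCOVA: about 6.5%; with Mann–Whitney also available, about 7%.
- With a dose-adjusted model as the alternative to the t-test: about 8.7%; with all of these available: about 10%.

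These figures move by a point or two with the assumed covariate strength and dose spread.

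**The case against.** The strongest defense is that section 2.6.1 can be read as simple comparisons first and adjusted models second. Including a covariate implies a regression-type model, SPSS and R both fit one, and a condensed article may leave the model's name to an analysis plan. The absence of the word ANCOVA is indeed no finding. But the two-step order is not written, the phrase "All analyses will control for age, sex, years of education" exempts nothing, and the double use of time estimation remains under either reading.

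The correlation part is weaker. Section 2.6.5 shows that partial correlations are intended somewhere, though for analyses that involve neural indices and not for the within-group correlations of 2.6.1.

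Choosing between t-test and Mann–Whitney by distribution is a common rule stated in advance, and is not an error in itself. A reader might infer that HCT accuracy will prove non-normal and so be sent to a test that admits no adjustment. The document says nothing about its distribution, and only the plain Mann–Whitney test lacks an adjusted form; rank ANCOVA and proportional-odds models exist.

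A reader might also infer that the unadjusted comparison is biased by education. Matching covers age and sex only, so this is possible, but the document gives neither an education difference nor its relation to HCT. No bias is shown.

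**Conclusion.** The contradiction stands, in a narrow form. Section 2.6.1 sets rules for the primary outcome that cannot all be followed, and does not determine whether the HCT comparison is adjusted or which covariates it carries. This is a conflict between stated rules, not missing detail.

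The effect on type I error is modest: about 6.5–7% for a choice between the unadjusted tests and the three-covariate ANCOVA, and about 9–10% once a dose-adjusted model is available. It arises only if the choice follows sight of the results, and nothing in the document says that it will. The larger practical consequence is the power difference caused by dose (80% against about 27–56% at d = 0.736), which rests wholly on the assumed dose distributions. None of this shows the planned sample size to be wrong. The matter should be settled before analysis.

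**What to change.** Reword section 2.6.1 so that it names one primary analysis: a linear model (ANCOVA) of HCT accuracy on group, age, sex and years of education, reporting the adjusted mean difference with its 95% confidence interval. If residuals are non-normal, keep the model and use robust standard errors or a permutation p-value. Label the t-test and Mann–Whitney results descriptive.

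Two covariates in the present text need an explicit decision, because this model omits them:

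- **Time estimation.** Put it in the primary model or in the sensitivity analysis, not both.
- **Chlorpromazine-equivalent dose.** It is in effect zero in all controls and largely collinear with group, so it is better examined within patients than in the between-group model. State this as a deliberate change from the present rule.

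Use the same adjusted model for MAIA, BPQ and cognition, and name partial correlations in 2.6.1 wherever adjustment is intended.

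The cost is a rewording, in software already listed, and three degrees of freedom (55 rather than 58; 54 if time estimation enters the primary model). The power loss is negligible if the covariates are balanced between groups and small if education is not.

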### Participants

2.3

Participants will include 30 individuals with schizophrenia and 30 age- and sex-matched healthy controls. The planned sample size was informed by effect sizes reported in our recent meta-analysis examining interoceptive accuracy in schizophrenia (17). That study reported a moderate effect size for group differences in interoceptive accuracy between individuals with schizophrenia and healthy controls. Based on this effect size, a sample of approximately 30 participants per group provides adequate statistical power (approximately 80%) to detect group differences at an alpha level of 0.05. In addition, sample sizes of approximately 25–35 participants per group are commonly reported in multimodal neuroimaging studies investigating schizophrenia. Therefore, the present sample size was considered appropriate for the behavioral objectives of this study.

Individuals with schizophrenia will be recruited from inpatient and outpatient units at Wuxi Mental Health Center and diagnosed by two senior psychiatrists according to DSM-5 criteria. Healthy controls will be recruited from the local community through advertisements and word-of-mouth and screened To ensure the absence of psychiatric, neurological, or major medical conditions. All participants will be right-handed, aged 18–65 years, and capable of providing written informed consent.

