Importantly, this study may also have clinical implications. By identifying specific brain regions and networks associated with interoceptive dysfunction, this study may help clarify the neural mechanisms underlying altered bodily self-processing in schizophrenia. Such mechanistic insights could inform the development and refinement of targeted interventions, including body-awareness-based and mindfulness-based approaches, which are thought to engage interoceptive and self-regulatory neural systems. In addition, identifying neural correlates of interoceptive deficits may help guide neuromodulation strategies by providing potential circuit-level targets for intervention and enabling more mechanistically informed and personalized treatment approaches.

Several considerations should be acknowledged. As a cross-sectional protocol, the study will not permit causal inferences regarding the directionality between interoceptive dysfunction and neural abnormalities. Although medication effects will be statistically controlled, they may still influence behavioral and neural outcomes. Antipsychotic medications may affect autonomic nervous system function, including heart rate and heart rate variability, which could potentially influence performance on interoceptive tasks such as the heartbeat counting task. Although medication dosage will be statistically controlled using chlorpromazine equivalents, residual medication-related effects cannot be completely excluded and should be considered when interpreting the findings.

Additionally, the relatively modest sample size may limit statistical power for detecting subtle neural effects or conducting reliable individual-level or subgroup analyses. Although the planned sample size is consistent with comparable multimodal neuroimaging studies, neuroimaging findings in this study should therefore be interpreted with caution. Accordingly, the primary analyses will focus on group-level comparisons and brain–behavior associations, which provide greater statistical robustness and are commonly used in neuroimaging research with similar sample sizes. Neuroimaging analyses in this protocol are primarily exploratory and will be interpreted cautiously with appropriate correction for multiple comparisons.

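### Chlorpromazine-equivalent dose is zero or unrecorded in every control, so adjusting the patient–control comparisons of Section 2.6.1 for it changes the contrast and costs power

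*Protocol article*

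**What the plan says.** The primary outcome is given as "Interoceptive accuracy, assessed using the heartbeat counting task (HCT"), and the first primary objective compares it between patients and matched controls. The Participants section fixes the size: "Participants will include 30 individuals with schizophrenia and 30 age- and sex-matched healthy controls". It claims that "approximately 30 participants per group provides adequate statistical power (approximately 80%) to detect group differences at an alpha level of 0.05".

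Section 2.6.1 lists HCT accuracy, time estimation, MAIA, BPQ and the cognitive tests as continuous variables that "will be compared using independent-samples t-tests or Mann–Whitney U tests for non-normal distributions". It then adds: "All analyses will control for age, sex, years of education, and medication dosage (chlorpromazine equivalents"). For the heartbeat task there is one more covariate: "In analyses involving HCT accuracy, time estimation performance will additionally be included as a covariate". Nothing limits the dose adjustment to patient-only analyses.

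Three other places determine what dose can be in each group:

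- Section 2.3.3 excludes controls with any psychiatric disorder in their lifetime.
- Section 2.4.2 collects "illness duration and medication status (patients only").
- Section 2.3.1 admits patients on a stable antipsychotic regimen and also medication-naive patients.

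The Discussion returns to the point: "Although medication dosage will be statistically controlled using chlorpromazine equivalents", residual medication effects cannot be ruled out.

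**The concern.** A covariate can adjust a group comparison only where the groups overlap on it. Here dose is zero by design in one group, or blank if the form is followed literally, and presumably positive in most of the other. This has two consequences for any model that contains both group and dose.

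First, the coefficient changes meaning. The dose slope is estimated from the 30 patients alone. The group term becomes the difference between controls and hypothetical patients at zero dose. Only medication-naive patients, if any enrol, give direct information at that point. The primary objective asks for the difference between people with schizophrenia and controls.

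Second, the standard error of the group term rises because dose and group carry much of the same information. The sample-size statement makes no visible allowance for this.

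The comparisons at stake are HCT accuracy and the MAIA, BPQ, time estimation and cognitive contrasts, wherever they are adjusted as the section directs.

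**Working it through.** **Inputs from the protocol article.** 30 per group; alpha 0.05 (sidedness not stated, two-sided taken here); power about 80%; effect size described only as moderate. No allowance for dropout is stated, and none is used.

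**Inferred.** Dose is 0 in all controls (Sections 2.3.3 and 2.4.2).

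**Assumed.** The article gives no dose distribution. Let patient dose have mean m and SD s, with CV = s/m. The main range is 0.5 to 1.0. A narrower spread of 0.3 is shown for reference. No true effect of dose on the outcome is assumed in the power figures.

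**Step 1: the stated power.** Noncentral t, df = 58, noncentrality d × √(30/2). Power of 80% requires d = 0.736 two-sided (0.65 one-sided). Because the article gives no number for the effect, its 80% can be neither confirmed nor refuted. The loss is therefore measured from the d that would give 80%, where the noncentrality is 0.736 × 3.873 = 2.85.

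**Step 2: what the group term estimates.** Let δ be the coefficient of group and β the coefficient of dose. The mean difference between patients and controls is δ + βm. The adjusted model reports δ, which is the difference at dose zero. The two agree only if β = 0.

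**Step 3: collinearity.** With 1:1 allocation and dose 0 in controls:

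- Var(group) = 1/4, Cov(group, dose) = m/4, Var(dose) = s²/2 + m²/4
- r² = (m/4)² / [(1/4)(s²/2 + m²/4)] = 1/(1 + 2CV²)
- VIF = 1/(1 − r²) = 1 + 1/(2CV²)

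For CV 0.5, VIF = 1 + 1/0.5 = 3.0. For CV 1.0, VIF = 1 + 1/2 = 1.5.

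**Step 4: power with dose in the model.** The noncentrality is divided by √VIF: 2.85/√3.0 = 1.64 and 2.85/√1.5 = 2.33.

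| CV of patient dose | r(group, dose) | VIF | SE multiplied by | Power at d = 0.736 | n per group to restore (30 × VIF) |
|---|---|---|---|---|---|
| 0.3 | 0.92 | 6.6 | 2.56 | 19% | 197 |
| 0.5 | 0.82 | 3.0 | 1.73 | 37% | 90 |
| 0.8 | 0.66 | 1.8 | 1.33 | 56% | 54 |
| 1.0 | 0.58 | 1.5 | 1.22 | 63% | 45 |

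At an assumed d of 0.5, power is 48% without dose and 20% to 34% with it (CV 0.5 to 1.0).

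**Step 5: medication-naive patients.** If 10% to 30% of patients are naive and CV among the treated is 0.4 to 0.6, VIF is 2.7 to 1.5 and power 40% to 62%.

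**Step 6: simulation.** With 10,000 runs per setting and gamma-distributed dose, power with dose in the model was 26%, 43% and 52% at CV 0.4, 0.6 and 0.8. Without dose it was 79% to 80%. The formula gives 28%, 44% and 56%, so it is slightly optimistic.

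**Step 7: without dose.** Adjusting for age, sex, education and time estimation costs 4 degrees of freedom. Power is 79.9% if these covariates are unrelated to group.

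**The case against.** The strongest reply is that the section names tests that accept no covariates. On that reading the main HCT test is an unadjusted t-test or Mann–Whitney test with adjusted analyses beside it, and it loses no power. The sample-size statement, which mentions no covariates, fits this. The reply stands to this extent: the loss belongs to the adjusted comparison, and a reader who infers that the primary test is bound to lose most of its power goes beyond the text. But the covariate sentence covers all analyses and follows directly on the group tests, so the section contradicts itself and cannot be left as it is.

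A reader might also infer that the imaging contrasts are affected. The rule stands in the behavioral section. The voxel-wise and TBSS comparisons list no covariates, and Section 2.6.5 mentions covariates without naming them.

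The size depends on an assumed dose spread. Naive patients are eligible and both inpatients and outpatients are recruited, so the spread could be wide. That is why a range is given. Power is below 80% throughout it.

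Two further inferences lack support. Nothing in the article shows that dose tracks severity among these patients. Nor do the calculations, which set the dose effect to zero, show that a real deficit would be misattributed to medication.

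Finally, the Discussion concedes residual medication effects. It does not mention the overlap of dose with diagnosis.

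**Conclusion.** The dose rule is wrong as written for patient–control comparisons of behavioral and questionnaire data. The change of contrast follows from the design and does not depend on the dose spread. The power figure does: about 37% to 63% in place of 80% for CV 0.5 to 1.0, at d = 0.736, two-sided, with no true dose effect. Confidence is high in the direction and moderate in the size.

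The collinearity is strong but not complete, so the adjusted model can be fitted if controls are coded as zero. If their dose is left missing, a complete-case fit drops every control. In correlations within the control group the covariate is constant and simply falls out, which is a minor point.

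**What to change.** 1. In Section 2.6.1, remove chlorpromazine-equivalent dose from all patient–control models.
2. Name a model that takes covariates for the adjusted group comparison, such as linear regression or ANCOVA. Adjust for age, sex and years of education, and keep time estimation for HCT accuracy as the plan already specifies. State how this model relates to the t-test or Mann–Whitney test and which of them is the primary analysis.
3. Examine dose only within the schizophrenia group: its association with HCT, MAIA and BPQ, and as a covariate in the patient-only symptom associations. Add a treated-versus-naive sensitivity analysis if numbers allow.
4. Describe the group contrast as patients as enrolled, expected to be mostly treated, versus controls. Calling it treated patients versus controls would be inaccurate, because naive patients are eligible.
5. Reword the Discussion so that it does not say medication is statistically controlled in the group comparison.

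This needs a few sentences in Section 2.6.1 and the Discussion, and no new data. The price is giving up the claim that the group comparison is controlled for medication, which this design cannot deliver.
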